#### Randomization procedure

Each participant will be randomized in a 1:1 ratio (stratified by gender) to either high-dose parenterally infused iron or oral iron supplements using a web-based randomisation tool (http://www.randomizer.at). Good clinical practice (GCP) compliance of this software was confirmed by the Austrian Agency for Health and Food Safety (AGES).

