### Statistical aspects

#### Sample size justification

The sample size calculation was performed by the Department of Medical Informatics, Statistics and Documentation of the Medical University of Graz. Using a two-group *t* test with a 0.05 two-sided significance level, a sample size of 86 participants in each group will have 90 % power to detect a difference in mean of 8 % in transferrin saturation (estimating a post-treatment transferrin saturation of 28 % and 20 % in the high-dose intravenous iron group and oral iron group, respectively, based on results by a similar treatment regimen in otherwise healthy women with postpartum anaemia [34]). Allowing for a dropout of 14 %, originally 200 participants were planned to be enrolled in the study. As the actual dropout rate was substantially lower (<3 %), the study will be terminated after complete study participation of 172 participants plus the number of dropouts.

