#### Statistical procedures

Statistical analyses of the results will be performed using the intention-to-treat and the per-protocol principles. All study participants who are randomised and included into the study will be analysed whether they take their study medication for the entire term (oral iron) or not or whether or not they miss the follow-up visit (visit 1). All primary and secondary outcome measures will be analysed and checked for normal distribution of the results. If there is a normal distribution of laboratory results, they will be analysed by the two-sided *t* test; if there is not a normal distribution they will be analysed by non-parametric tests like the Wilcoxon test for related samples or the Mann-Whitney U test for comparison of independent samples. The significance level will be set to *p* < 0.05. Data will be presented as mean ± standard deviation or median (interquartile ranges) as appropriate. For missing data, no imputation will be performed. A statistical evaluation will be performed using the software program SPSS for Windows (IBM SPSS Inc., Chicago, IL, USA).

A predefined subgroup analysis will separately analyse participants with a baseline ferritin of ≤15 ng/ml. The Department of Blood Group Serology and Transfusion Medicine, Medical University of Graz, will maintain responsibility for the final trial dataset.

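### An undefined normality check on the observed outcome chooses the primary test and summary measure, although the trial is sized on a difference in means

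*Protocol article*

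**What the plan says.** Three places in the protocol article matter.

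- **Outcomes, Primary endpoint.** The endpoint is the between-group difference in transferrin saturation at visit 1. No summary measure (mean or median) is attached to it.
- **Sample size justification.** The method is a t test for two independent arms at the two-sided 5 % level. With 86 people per arm, the claim is "90 % power to detect a difference in mean of 8" percentage points. The basis is "estimating a post-treatment transferrin saturation of 28 % and 20 % in the high-dose intravenous iron group and oral iron group, respectively". No SD is given.
- **Statistical procedures.** Every outcome, the primary one included, is first examined for normality. Laboratory values judged normal go to a t test. For the other case the text reads: "if there is not a normal distribution they will be analysed by non-parametric tests like the Wilcoxon test for related samples". Those words end at a paired test. The same sentence goes on to name the Mann-Whitney U test for independent groups, and that is the branch that applies to the primary comparison. Results are then shown either as means with SDs or as medians with interquartile ranges. The article names no normality test, no threshold, and no target for the check (each arm, pooled values or residuals).

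**The concern.** The quantity used for sizing and the quantity that will be tested may differ, and the observed outcome data decide whether they do. If the check passes, the trial compares means. If it fails, the trial asks whether values in one arm tend to be higher than in the other, and reports medians. The second branch gives no estimate of the 8-point difference behind the sample size. Because the check is undefined, two analysts with the same data could follow different branches, and both would comply with the text.

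At stake is how the primary result may be read. With skewed data whose shape differs between arms, a significant Mann-Whitney result can occur when the means are equal.

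**Working it through.** **1. Reproduce the sample size and recover the SD.** Inputs from Sample size justification: difference 28 − 20 = 8 points, 86 per group, two-sided 0.05, power 90 %. The SD is missing, so it is solved for.

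- Normal approximation: SD = 8 × √(86/2) / (1.960 + 1.282) = 8 × 6.557 / 3.242 ≈ 16.2.
- t test (noncentral t): standardised difference 0.497, so SD = 8 / 0.497 ≈ 16.1. Any SD from 16.00 to 16.09 rounds up to 86 per group.
- Forward check with SD 16: 86 per group, power 90.3 %. Dropout: 172 / 0.86 = 200, as stated.

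The stated figures agree with each other at an SD of about 16. As the SD was back-solved, this shows consistency and does not verify the SD.

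**2. Can an outcome with these figures be normal?** Transferrin saturation cannot be negative. Under normality:

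- oral: P(value < 0) = Φ(−20/16) = Φ(−1.25) = 10.6 %, about 9 of 86;
- intravenous: Φ(−28/16) = Φ(−1.75) = 4.0 %, about 3 of 86.

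So these means and this SD imply right-skewed data.

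**3. How often would the rule switch?** Assumptions (not in the article): Shapiro-Wilk at 0.05 in each arm, with a switch if either arm fails; 86 per arm; simulated trials.

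- SD 16, means 20 and 28: about 100 % for lognormal, gamma, beta, Weibull and zero-truncated normal data; about 10 % for truly normal data.
- SD 10, same means: 62 % (Weibull), 86 % (beta), 98 % (gamma), 100 % (lognormal).

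**4. Power.**

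- Equal SDs of 16, skewed shapes: t test 89–90 %, Mann-Whitney 95–99.5 %.
- SD rising with the mean (13.2 and 18.4, about the same pooled variance): t test 90–92 %, Mann-Whitney 80–95 %.

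**5. Rejection when the means are equal.** Both means 24 (midway between 20 and 28), 8,000 trials per cell, all SD pairs assumed:

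| SDs | Rule, lognormal | Rule, gamma | Rule, normal | Welch, all three shapes |
|---|---|---|---|---|
| 16 v 16 | 4.7 % | 4.5 % | 5.3 % | 4.7–5.3 % |
| 16 v 10 | 25.0 % | 18.5 % | 5.1 % | 4.8–5.5 % |
| 16 v 12 | 13.4 % | 11.3 % | 5.2 % | 4.9–5.0 % |
| 10 v 8 | 7.7 % | 6.4 % | 4.9 % | 4.6–5.3 % |

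Repeat runs with other seeds moved the larger entries by about one percentage point.

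**6. Why the excess arises.** A lognormal median is mean / √(1 + (SD/mean)²). For SD 16 it is 24 / √1.444 = 19.97, and for SD 10 it is 24 / √1.174 = 22.15. The means are equal but the medians are not, so Mann-Whitney responds to a real tendency of one arm to be higher. The normal column shows that unequal spread without skew leaves rejection near 5 %.

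**The case against.** Several objections have force.

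- **The endpoint is not defined as a mean difference.** This stands. Only the sample size paragraph speaks of means, so Mann-Whitney does not contradict the stated endpoint. The mismatch is with the quantity that justified 86 per group.
- **The rule is written in advance and both branches are named.** True, but the condition that selects the branch is undefined and depends on the outcome data. A separate analysis plan might define the check. The published rule would still let the data choose the test.
- **The SD of 16 is inferred.** This stands. The planning means come from women with postpartum anaemia, not donors, so the donors' SD may be smaller. A visual check would also be less predictable than Shapiro-Wilk. A switch is likely under a formal test, not certain.
- **The unequal SDs are invented.** They are an illustration. Nothing in the article gives SDs by arm, and the excess shrinks to 6–8 % at 10 v 8.

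A reader might also infer that the planned power is lost, that the type I error is inflated in general, or that Mann-Whitney reacts to spread alone. The calculations support none of these. With skewed data and equal SDs, Mann-Whitney has more power than the t test. With identical distributions the rule stays near 5 %. With unequal spread and no skew it also stays near 5 %. The 19–26 % is an error rate only for a claim about means.

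**Conclusion.** The point holds as a defect in how the primary analysis is fixed. An undefined check on the observed outcome selects both the test and the summary measure, while the trial is sized on a difference in means. If the SD is near the implied 16 and a formal normality test is used, the Mann-Whitney branch is the likely one, and it does not estimate the 8-point difference.

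The consequence is one of interpretation. If the arms have equal means but differently shaped skewed distributions, rejection can exceed 5 %: about 19–26 %, 11–13 % or 6–8 % for the three assumed SD pairs. A significant result from that branch could not then be read as a difference in mean transferrin saturation. The size depends on the assumed shapes and SDs. The structural fault, a primary test left to the data, depends on neither. It does not undermine the sample size, and it is worth correcting before the outcome is analysed.

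**What to change.** For the primary endpoint, remove the normality check and name one analysis of the mean difference in advance. Welch's t test is the simplest. The alternative is ANCOVA adjusted for visit 0 transferrin saturation and gender (the stratification factor) with robust standard errors. It needs transferrin saturation to have been measured in the visit 0 sample, because the article describes that sample without listing its assays. Report the mean difference with its 95 % CI as the primary result. Keep Mann-Whitney, with medians, as a named sensitivity analysis. State the SD used for the sample size.

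The cost is wording only. The sample size stays at 86 per group, since Welch's test keeps about 89–90 % power in the skewed lognormal and gamma scenarios at SD 16. Completed recruitment is no obstacle if the change is made and dated before the outcome is analysed. The downside is that, with skewed data, the p-value may be less favourable than Mann-Whitney's.

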### Data and safety monitoring

All laboratory analyses are stored on password-protected secure servers and will only be accessible for authorized individuals from the Medical University of Graz. Clinical data are collected through paper-based CRFs. The CRFs are confidential documents and held securely at the Department of Blood Group Serology and Transfusion Medicine. Each participant is assigned a trial identity code number to anonymize documented CRF data.

In the CRF of the follow-up visit (visit 1), the participants are asked for possible drug-related adverse events. Furthermore, all participants are requested to promptly report possible adverse events by telephone. The study participants receive telephone contact numbers from the study team at the time of inclusion (visit 0).

### Subject recruitment

In Styria, annually about 60.000 units of whole blood are collected at mobile and stationary locations by the Red Cross and further processed to packed red blood cell concentrates, pooled platelet concentrates and fresh frozen plasma at the Department of Blood Group Serology and Transfusion Medicine of the Medical University of Graz. Approximately 1200 single donor platelet apheresis collections are performed in our department per year. A number of different commercial plasma collection centres in the region offer the opportunity to donate apheresis plasma.

Depending on the region of residence, we estimate that 5000 to 10,000 donors are potential participants of this study. Of those, 1000 to 2000 may fulfil the inclusion and exclusion criteria; thus, we need to recruit 10–20 % of all potential participants. We aim to recruit two blood donors per week for this trial.

The University Hospital of Graz (“LKH-Universitätsklinikum Graz”) is a large tertiary care facility with 7200 employees. It is the teaching hospital for one of the three public Medical Universities in Austria. The catchment area covers the entire southeast of Austria (approximately 2 million people). Currently 1413 beds at general wards and 112 intensive care unit (ICU) beds are available. Each year, approximately 80,000 patients are treated as inpatients and 440,000 as outpatients.

### Specific gender relevance of the project

Adverse reactions related to blood donation are more common in females, which is one of the major reasons why more men become regular donors [35]. In particular, iron deficiency caused by blood donation is highly prevalent in premenopausal female donors because of lower blood volume, higher requirements, and greater losses during menstrual bleeding, pregnancies, birth, and lactation [6, 8, 9, 36, 37]. The estimated iron loss from one whole blood donation corresponds to approximately 10 % of total body iron and 66–97 % of the total iron stores of a premenopausal woman [38, 39].

More importantly, unrecognized and therefore untreated iron deficiency has been linked to adverse pregnancy outcomes such as preterm delivery and lower weight babies [40]. Particularly in the subgroup of premenopausal females, a regular evaluation of donor iron status should be considered or the donation intervals prolonged.

#### Study participation for premenopausal women

There are no data available on foetal toxicity of ferric carboxymaltose, so the application of this drug during the early stages of pregnancy is contraindicated. Therefore, women of childbearing age are only allowed to participate in this trial when pregnancy has been excluded by urinary β-HCG testing at the beginning of the study and is repeated by the participants in the intervention phase. Lactating women are excluded from blood donation and therefore are also not targeted in this study.

### Ethical aspects

The approval of the institutional ethical committee was given in June 2013 (EK 25–345 ex 12/13) and has been renewed yearly.

### Registration at clinical trials

This trial was registered at ClinicalTrials.gov in February 2013 (Clinical Trials Identifier: NCT01787526).

## Discussion

Iron deficiency anaemia occurs when iron stores have been consumed [1]. Before establishment of anaemia, iron deficiency may have other, more subtle and unspecific adverse effects on an individual such as decreased physical and cognitive performance [41, 42]. Since iron is an important element in many enzymes, deficiency may affect various cellular processes like DNA synthesis [43], mitochondrial energy metabolism [44], and the immune system [45]. Therefore, blood donation establishments should focus on donors at risk for iatrogenic iron deficiency without anaemia and develop strategies for its prevention. Although the benefit of iron therapy in subjects without anaemia remains controversial, mainly due to a lack of large randomised clinical trials for truly deficient subjects, a few studies have reported interesting results. For example, iron supplementation reduced unexplained fatigue in otherwise healthy women with iron deficiency and improved verbal learning and memory in adolescent girls [15, 46]. Iron deficiency has additionally been found to be associated with restless legs syndrome, and iron therapy improved symptoms significantly in blood donors [47]. Recently, it was shown that the recovery of blood donors’ iron stores receiving oral iron supplementation after blood donation took a median of 76 days compared to a median recovery time of longer than 168 days for study participants not taking iron [13], also questioning the current relatively short donation intervals of 2–3 months.

So far, no randomised controlled trial has compared high-dose intravenous iron to oral iron supplementation in blood donors with iron deficiency. Intravenous iron may be an excellent option in this setting. If our study can establish that intravenous iron is feasible in blood donors and the substantial impediments like costs and logistics can be overcome, high-dose intravenously infused iron given immediately after whole blood or apheresis donation through the present venous access could be a very efficient way for correction and/or prevention of iatrogenic iron deficiency. Such an approach could protect blood donors from symptoms related to iron deficiency and help to maintain an iron-replete blood donor pool.

### Trial status at the time of initial manuscript submission

Recruitment for this trial is ongoing.

## Abbreviations

AGES: Austrian Agency for Health and Food Safety
CRF: Case report form
GCP: Good clinical practice
ICU: Intensive care unit
IV: Intravenous
PO: Peroral
β-HCG: Beta-human chorionic gonadotropin
